## Methods and analysis

2

### Study design and context

2.1

The present document outlines the research protocol for an analytical observational, comparative cross-sectional study. The study will be conducted in the cities of Quito and Riobamba, which are located in the Highlands of Ecuador. Data collection is planned to start in the fourth trimester of 2025 and end the fourth trimester of 2026. Data analysis is planned to start in the first trimester of 2026 and end the fourth trimester of 2028. A pilot study involving 10 autistic and NA children will be conducted during the third trimester of 2025 to refine procedures and instruments. The overall study design and procedures are summarized in **Supplementary Figure 1**.

### Study population, selection criteria and sample size

2.2

#### Group A - autistic children

2.2.1

This group includes children and adolescents aged 3 to 17 years (n = 100), from diverse socioeconomic backgrounds, who have been previously diagnosed with autism by certified physicians following the Ecuadorian Clinical Practice Guide and was based on the DSM-5 criteria (23). At least 100 participants are required, but we will accept up to 150 children.

*Inclusion criteria*

Age between 3 and 17 years.Previous autism diagnosis by a neurologist or psychiatrist after meeting the DSM-5 diagnostic criteria for autism. Such diagnosis will include the following International Classification of Diseases, 10th Edition (ICD-10) categories: F84.0 (Childhood autism), F84.5 (Asperger’s syndrome), F84.8 (Other pervasive developmental disorders), and F84.9 (Pervasive developmental disorder, unspecified).

*Exclusion criteria*

Inability to sit and/or stand independently.

#### Group B - non-autistic children without neurodevelopmental disorders

2.2.2

This group will include children and adolescents aged 3 to 17 years (n = 100), from the general population with age and gender distribution similar to the autistic group.

*Inclusion criteria*

Age between 3 and 17 years.

*Exclusion criteria*

A 10-item Autism Spectrum Quotient (AQ-10) score of 6 points or higher.A Parent’s Observations of Social Interactions (POSI) score of 3 points or higher.History of diagnosis, therapy, or treatment for any neurodevelopmental disorder coded under ICD-10 F84.Inability to sit and/or stand independently.

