#### Group C - non-autistic children with other neurodevelopmental disorders

2.2.3

This group will include children and adolescents aged 3 to 17 years (n = 100) diagnosed with intellectual, psychological, emotional, or behavioral developmental disorders not including autism.

*Inclusion criteria*

Age between 3 and 17 years.Diagnosis with psychological developmental disorders (ICD-10 F80-F89), which includes: F80 (specific developmental disorders of speech and language), F81 (specific developmental disorders of school skills), F82 (specific developmental disorder of motor function), F83 (mixed specific developmental disorders), F88 (other disorders of psychological development) and F89 (unspecified disorder of psychological development). Diagnosis with intellectual disabilities (ICD-10 F70-F79), including F70 (mild mental retardation), F71 (moderate mental retardation), F78 (other mental retardation), F79 (unspecified mental retardation). Diagnosis with emotional and behavioral disorders usually occurring in childhood and adolescence (ICD-10 F90-F98), which includes F90 (hyperkinetic disorders), F91 (conduct disorders), F92 (mixed disorders of conduct and emotions), F93 (emotional disorders with onset specific to childhood), F94 (disorders of social functioning with onset specific to childhood), F95 (tic disorders), and F98 (other emotional and behavioral disorders that commonly occur in childhood and adolescence).

*Exclusion criteria*

AQ-10 score of 6 points or higher.POSI score of 3 points or higher.Diagnosis with or report of having received therapy or treatment for a neurodevelopmental disorder coded as ICD-10 F84.Being unable to sit and/or stand autonomously.

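### The written criteria for Group B exclude only ICD-10 F84, so a child with a Group C diagnosis can enter the group described as free of neurodevelopmental disorders

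*Protocol article*

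**What the plan says.** All references are to the protocol article.

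- **Group B (2.2.2).** The heading reads "Group B - non-autistic children without neurodevelopmental disorders". The children come "from the general population with age and gender distribution similar to the autistic group". The only inclusion criterion is age 3 to 17 years. The exclusions are "A 10-item Autism Spectrum Quotient (AQ-10) score of 6 points or higher"; "A Parent’s Observations of Social Interactions (POSI) score of 3 points or higher"; "History of diagnosis, therapy, or treatment for any neurodevelopmental disorder coded under ICD-10 F84"; and inability to sit and/or stand independently.
- **Group C (2.2.3).** These are children "diagnosed with intellectual, psychological, emotional, or behavioral developmental disorders not including autism". The qualifying codes fall in the ranges F80-F89 (itemised as F80 to F83, F88 and F89), F70-F79 (itemised as F70, F71, F78 and F79) and F90-F98. The exclusions are the same AQ-10 and POSI cut-offs, diagnosis of or treatment for an F84 disorder, and inability to sit and/or stand.
- **Sample size (2.2.4).** The calculation compares Group A (0.57) with Group B (0.37) and gives 94 per group, raised to 100 for 5% non-response.
- **Use of the groups.** Section 4.1 presents autistic children, NA children and children with other developmental disorders as three separate groups. The Abstract counts Groups B and C together as 200 NA peers.

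**The concern.** The heading of 2.2.2 describes one population and the criteria beneath it admit a wider one. Recruiters apply the criteria. The diagnostic exclusion names F84 explicitly, so read as written it leaves every Group C code eligible for Group B.

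Group membership is the exposure in this study. Section 4.1 relies on the three-group structure to show what is specific to autism. If some children with other developmental disorders are recorded in B, then B and C become more alike. The A versus B comparison would then be made against a reference group that is not the one described. Section 4.2 adds to the concern: it says that cognitive level can influence diet independently of sensorimotor differences, and that no formal cognitive assessment will be done. A child with an intellectual disability in Group B would therefore not be picked up by a study measurement of cognition.

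**Working it through.** **Step 1: compare the criteria.**

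| Criterion | Group B | Group C |
|---|---|---|
| Age 3-17 | required | required |
| Qualifying diagnosis in F70-F79, F80-F89 (not F84) or F90-F98 | neither required nor excluded | required |
| AQ-10 of 6 or more | excluded | excluded |
| POSI of 3 or more | excluded | excluded |
| F84 diagnosis, therapy or treatment | excluded | excluded |
| Unable to sit and/or stand | excluded | excluded |

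The lists differ in one row only, and there Group B is silent. Every child eligible for C therefore also meets the written criteria for B. The two screens do not separate the groups: sections 3.5.2.1 and 3.5.2.2 describe them as measures of autistic traits, and they apply equally to both. Section 2.4 collects health status, treatments and therapies from caregivers, but no section uses that information to exclude a Group B child or move the child to C.

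**Step 2: reproduce the stated sample size.** By the formula in 2.2.4:

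n = (1.96 + 0.84)² × [0.57×0.43 + 0.37×0.63] / 0.20² = 7.84 × (0.2451 + 0.2331) / 0.04 = 93.7, rounded up to 94.

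The stated figure reproduces. With 100 recruited and 5% lost, 95 per group are evaluable. The same unpooled variance then gives a standard error of √[(0.2451 + 0.2331)/95] = 0.0709 and power Φ(0.20/0.0709 − 1.96) = Φ(0.859) = 80.5%.

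**Step 3: illustrate overlap.** Let c be the share of Group B with a Group C diagnosis and p_C the malnutrition prevalence in such children. Neither is in the document; both are assumed here. If the remaining Group B children are at 0.37:

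- p_B = (1 − c) × 0.37 + c × p_C
- A-B difference = 0.57 − p_B
- C-B difference = (1 − c) × (p_C − 0.37)

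| p_C | c | p_B | A-B difference | C-B difference | A-B power, 95 per group |
|---|---|---|---|---|---|
| 0.37 | any | 0.37 | 0.20 | 0 | 80.5% |
| 0.47 | 10% | 0.38 | 0.19 | 0.09 (from 0.10) | 76.1% |
| 0.47 | 20% | 0.39 | 0.18 | 0.08 (from 0.10) | 71.4% |
| 0.57 | 10% | 0.39 | 0.18 | 0.18 (from 0.20) | 71.4% |
| 0.57 | 20% | 0.41 | 0.16 | 0.16 (from 0.20) | 60.8% |

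Any C-B difference shrinks by the factor (1 − c). The A-B difference shrinks only if p_C is above 0.37; if p_C were below 0.37 it would widen.

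**Step 4: check the baseline.** Section 2.2.4 takes 0.37 from a national survey of Ecuadorian children and states no exclusion of developmental disorders. It may already be a mixed-population rate. If it contained 20% of children at 0.47, the rest would be at (0.37 − 0.2×0.47)/0.8 = 0.345. A Group B with that same mix would sit at 0.37 and have the planned power, and a Group B restricted to children without these disorders would have about 89% at 95 per group. The table in step 3 is therefore one scenario and not a measured loss against plan.

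**The case against.** The strongest reply is that the intent is clear. The heading is part of the definition, Group C is titled as the group with other disorders, and section 4.1 lists three distinct groups. Health and therapy data are collected at visit 1, so the team could allocate children correctly. This stands to the extent that overlap is possible but not shown. It does not remove the contradiction, because no written rule carries the intent into eligibility or tells staff to use those data.

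A reader might infer that all the group contrasts are contaminated. The document does not support that. Every Group C child still needs a Group C diagnosis, so A versus C is not affected. Specific objectives 1 to 3 in the Introduction compare autistic children with NA peers, and the Abstract's NA total includes both B and C. In that pooled comparison, recording a child in B rather than C moves the child within the NA set and adds no autistic child. B versus C is neither a named objective nor powered.

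A reader might also infer that the study is underpowered. That does not follow either: the overlap share and p_C are both assumed, p_C = 0.37 gives no loss, and the 37% may already include these children.

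**Conclusion.** The point holds as an eligibility rule that contradicts the group it defines. As written, Group B can include children with Group C diagnoses. The consequence is a blurred B versus C distinction and, where those children differ from other Group B children in malnutrition, diet, microbiota or sensorimotor measures, a biased A versus B comparison.

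The size is unknown. For the malnutrition comparison, 20% overlap and 95 per group give power between about 80% (p_C = 0.37) and about 61% (p_C = 0.57). These figures assume that the rest of Group B is at exactly 0.37 and are illustrative only. The stated 94 and 100 per group are not shown to be wrong. The correction is still worth making, because it concerns the definition of the reference group in the comparison that sizes the study, and it costs very little.

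**What to change.** In section 2.2.2, extend the diagnostic exclusion to a history of diagnosis, therapy or treatment for any disorder coded ICD-10 F70-F79, F80-F89 (including F84) or F90-F98. Add one sentence stating that a child with a qualifying Group C diagnosis is assigned to Group C, never to Group B, on the basis of the caregiver health and therapy questionnaire given at visit 1. Any child already enrolled in Group B can be checked against the same rule.

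The cost is one or two sentences and, if the questionnaire does not already ask about these diagnoses, one added item. The sample size does not change. Some children will move from B to C. A few with therapy or treatment but no qualifying diagnosis will fit neither group. Section 2.2.3 should also say whether the ranges or the itemised codes govern, because codes inside F70-F79 that are not itemised would otherwise be left without a group.

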#### Group C - non-autistic children with other neurodevelopmental disorders

2.2.3

This group will include children and adolescents aged 3 to 17 years (n = 100) diagnosed with intellectual, psychological, emotional, or behavioral developmental disorders not including autism.

*Inclusion criteria*

Age between 3 and 17 years.Diagnosis with psychological developmental disorders (ICD-10 F80-F89), which includes: F80 (specific developmental disorders of speech and language), F81 (specific developmental disorders of school skills), F82 (specific developmental disorder of motor function), F83 (mixed specific developmental disorders), F88 (other disorders of psychological development) and F89 (unspecified disorder of psychological development). Diagnosis with intellectual disabilities (ICD-10 F70-F79), including F70 (mild mental retardation), F71 (moderate mental retardation), F78 (other mental retardation), F79 (unspecified mental retardation). Diagnosis with emotional and behavioral disorders usually occurring in childhood and adolescence (ICD-10 F90-F98), which includes F90 (hyperkinetic disorders), F91 (conduct disorders), F92 (mixed disorders of conduct and emotions), F93 (emotional disorders with onset specific to childhood), F94 (disorders of social functioning with onset specific to childhood), F95 (tic disorders), and F98 (other emotional and behavioral disorders that commonly occur in childhood and adolescence).

*Exclusion criteria*

AQ-10 score of 6 points or higher.POSI score of 3 points or higher.Diagnosis with or report of having received therapy or treatment for a neurodevelopmental disorder coded as ICD-10 F84.Being unable to sit and/or stand autonomously.

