**Methods:**

This comparative cross-sectional study will recruit 100 autistic children and adolescents (aged 3–17 years) and 200 age-/sex-matched NA peers (including 100 with developmental disorders other than autism). Autism severity will be assessed using the Childhood Autism Rating Scale; NA peers will be screened with the Autism Spectrum Quotient-10. Dietary intake will be evaluated via three 24-hour dietary recalls, supplemented by questionnaires on socioeconomic status, health, and medications. Nutritional status (anthropometry, bioimpedance) and gut microbiota composition and diversity will be assessed. SMD proxies (sensory gating, sensory adaptation) will be measured using a smartphone application.

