### Recruitment and patient involvement

2.3

This study protocol was designed in collaboration with a special education school in Quito and a child neurodevelopment center in Riobamba. Both are private centers where autistic children and adolescents receive rehabilitation services. Additional participants will be recruited through posters and flyers distributed on social networks, at educational institutions, and through associations of autistic children’s parents. Children in Group B will be recruited from the family networks of Group A participants and matched for sex and age with their autistic peers. The target ratio between Groups A and B is approximately 1:2. During the development of the protocol, parents and professionals from recruitment sites provided valuable recommendations about the recruitment process, procedures and study goal.

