#### Neurophysiological assessment

3.5.4

Neurobehavioral assessments will be performed using a smartphone-based platform (21). The assessment will include a general measurement of spontaneous and stimulus-evoked postural, head, facial, and vocal responses, along with specific neurometric tests, including PPI and SH. During the experiment, children will use wired headphones to watch an audio-normalized video on a smartphone. The application delivers auditory stimuli, and the participant’s responses are captured using the smartphone’s front-facing camera at 60 frames per second.

Two audio-normalized videos will be used: one for younger children (aged 3–5 years), featuring a compilation of moving shapes and animals, and one for older children (aged 6 years and older), which depicts a basic storyline of a boy and a girl playing a video game. Both videos are devoid of any language content. The videos are audio-normalized by adjusting the audio track to ensure its peak level does not exceed approximately 60–70 decibels (dB).

While the participant watches the video, computer vision algorithms are used to track and record the position of the participant’s facial landmarks over time. The individual eyeblink traces will be analyzed with custom software developed in R. Eyelid position is calculated based on the tracked facial landmarks. Eyeblink traces are filtered and normalized as previously described (22). From valid normalized trials, we will extract the following three outcome measures: (i) PPI, (ii) SH, and (iii) general motor behavior.

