Self-medication represents an important limitation that our study will address. In Ecuador, self-medication, particularly with antibiotics, is common across various demographic groups (75). Excluding participants based on reported medication use would severely constrain recruitment. We will therefore account for this potential confounder by adjusting for medication use in multivariable statistical models when examining associations between gut microbiota composition and other outcomes. Specifically, medication use will be included as a covariate in linear models for alpha-diversity analyses and in PERMANOVA for beta-diversity comparisons. Finally, following previously used approaches (76), we will evaluate the robustness of our findings through sensitivity analyses that leverage the detailed medication data collected, exploring drug dosage, the specific reason for medication, and the prescribing source.

Another potential limitation of our study is that no formal cognitive ability assessment will be conducted. Cognitive level can influence dietary patterns independently of sensorimotor differences, for example, by affecting a child’s ability to express food preferences or aversions. Moreover, 30–40% of children with ASD also have co-occurring intellectual disability, a rate substantially higher than among NA peers (77). To address this potential confounding, we will use CARS scores as a proxy for phenotypic severity within the ASD group. Although CARS does not measure cognitive ability directly, it correlates with functional impairment and will allow us to explore whether associations differ by severity level. Nevertheless, residual confounding by unmeasured cognitive differences cannot be entirely ruled out.

The broad age range (3–17 years) of our sample represents another limitation, given the significant developmental heterogeneity within this period. While a narrower range would reduce variability, it would also compromise sample size and generalizability. To address this, age will be included as a covariate in all multivariate models to adjust for its potential confounding effects. Additionally, we have selected age-appropriate instruments to ensure that measurements are sensitive to developmental stages. Nevertheless, residual age-related variability may still influence our findings, and we acknowledge this trade-off.

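### The abstract calls all 200 non-autistic peers age- and sex-matched, but the methods give Group C no matching rule; for the smartphone outcomes, a linear age term alone may leave residual confounding

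*Protocol article*

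**What the plan says.** - Abstract, Methods: the comparison children are "200 age-/sex-matched NA peers (including 100 with developmental disorders other than autism"). The parenthesis places Group C inside the matched set.
- Section 2.2.2: Group B is to be drawn from the general population "with age and gender distribution similar to the autistic group".
- Section 2.3: "Children in Group B will be recruited from the family networks of Group A participants and matched for sex and age". The next sentence reads "The target ratio between Groups A and B is approximately 1:2".
- Section 2.2.3: "This group will include children and adolescents aged 3 to 17 years (n = 100) diagnosed with intellectual, psychological, emotional, or behavioral developmental disorders". What follows is a list of diagnoses and exclusions. Neither this section nor section 2.3 names a matching or distribution rule for Group C.
- Abstract, Analysis, and section 4.2: age, sex, socioeconomic status and medication use are planned covariates, and "age will be included as a covariate in all multivariate models". The form in which age enters is not stated.
- Section 3.5.4: "Two audio-normalized videos will be used: one for younger children (aged 3–5 years"), with a second video from age 6. The rule is the same in every group.

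**The concern.** Matching is a recruitment property. If it is claimed for Group C but not carried out while Group C is enrolled, it cannot be added afterwards. Group C is the comparison that separates what is specific to autism from what goes with developmental disorder in general, a purpose that section 4.1 claims for the three-group design. If its age mix drifts from that of Group A, the abstract describes a design that was not run, and the A–C contrast depends on model adjustment.

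For most outcomes, adjustment for age and sex is a reasonable second line. The smartphone outcomes (prepulse inhibition, startle habituation, general sensorimotor behaviour) are different because the viewing material changes abruptly at age 6. If the video shifts the response, the relation with age has a step there. A straight line in age does not follow a step, and what it misses falls partly on the group term when the groups differ in the share under 6.

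**Working it through.** **1. The places side by side**

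| Place | Group B | Group C |
|---|---|---|
| Abstract, Methods | matched | matched (explicitly included) |
| Section 2.2.2 / 2.2.3 | similar age and gender distribution | no rule |
| Section 2.3 | matched on sex and age | not named |

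The 1:2 ratio does not settle the matter. With 100 in A and 100 in B the ratio is 1:1. It becomes 1:2 only if Group B in that sentence means all 200 non-autistic peers. That reading conflicts with n = 100 for Group B in section 2.2.2, and recruitment through autistic children's family networks fits a diagnosis-defined group poorly.

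**2. The plan's own figure**

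The section 2.2.4 formula gives (1.96 + 0.84)² × [0.57 × 0.43 + 0.37 × 0.63] / 0.20² = 7.84 × 0.4782 / 0.04 = 93.7, so 94 as stated. Then 94 / 0.95 = 98.9, which the plan rounds to 100. The calculation concerns A versus B and does not involve matching, so this point changes no stated sample size.

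**3. How much a linear age term could leave behind**

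From the plan: 100 per group, ages 3 to 17, video change at age 6, age as a covariate.

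Assumed: Group A uniform from 3 to the 18th birthday (3/15 = 20% under 6), residual SD 1, no true A–C difference, a video step of δ SD, age entered linearly, and several age mixes for Group C.

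Let V = 1 if under 6. The large-sample bias in the C minus A difference is

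bias = δ × [ΔV − b × ΔAge], with b = [cov_A(V, age) + cov_C(V, age)] / [var_A(age) + var_C(age)].

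Group A: mean age 10.5; variance 15²/12 = 18.75; covariance 0.2 × (4.5 − 10.5) = −1.2.

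- *Group C uniform over 6–12:* mean 9, variance 6²/12 = 3, covariance 0. b = −1.2 / 21.75 = −0.0552. Bias = δ × [−0.2 − (−0.0552)(−1.5)] = −0.283δ, so −0.14 SD at δ = 0.5.
- *Group C with 10% under 6, the rest uniform over 6–18:* mean 0.1 × 4.5 + 0.9 × 12 = 11.25; variance 0.1 × 0.75 + 0.9 × 12 + 0.1 × 6.75² + 0.9 × 0.75² = 15.94; covariance 0.1 × (4.5 − 11.25) = −0.675. b = −1.875 / 34.69 = −0.0541. Bias = δ × [−0.1 + 0.0541 × 0.75] = −0.059δ, so −0.03 SD at δ = 0.5.

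Simulation at δ = 0.5 (4,000 runs, 100 per group), bias in SD, with two-sided 5% type I error in brackets:

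| Group C ages | Unadjusted | Linear age | Linear age + video |
|---|---|---|---|
| Same as Group A | 0.002 (5.0%) | 0.002 (5.2%) | 0.002 (5.1%) |
| 10% under 6 | −0.053 (6.4%) | −0.033 (5.3%) | −0.003 (4.7%) |
| 40% under 6 | 0.102 (10.9%) | 0.045 (6.1%) | 0.002 (5.1%) |
| 6–18 only | −0.106 (11.4%) | −0.076 (8.2%) | −0.005 (5.6%) |
| 6–12 only | −0.097 (9.6%) | −0.138 (14.6%) | 0.004 (4.4%) |

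Across the unequal mixes, linear adjustment leaves 0.01–0.09 SD at δ = 0.3 (type I error 5–9%) and 0.05–0.23 SD at δ = 0.8 (6–34%). For scale, the standard error of an unadjusted A–C difference is √(1/100 + 1/100) = 0.14 SD. In the 6–12 case linear adjustment is worse than none. With the video indicator, bias is about zero and type I error 4–6% throughout.

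**The case against.** A reader might infer that the age covariate cannot repair the lack of matching because of the two videos. The documents do not support that. The video is assigned by age alone and identically in every group, so any age adjustment that allows a step at 6 removes the problem without matching. The linear form is an assumption: section 4.2 names no form, section 3.6.2 foresees linear and nonlinear models, and section 4.2 promises sensitivity analyses and concedes residual age-related variability. The coding of age may properly be left to an analysis plan that is not shown. All of this stands, and the video term is therefore a recommendation, not a missing item.

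A reader might also infer that Group C will contain few children aged 3–5. Section 2.2.3 does not show this. It names 17 diagnostic codes, of which only three (F81, F91, F92) concern school skills or conduct; others, such as speech and language or motor disorders, carry no such suggestion, and entry is from age 3. The mixes with nobody under 6 are extremes. With partial imbalance the bias at δ = 0.5 is only 0.03 to 0.05 SD. No video effect of any size is documented, and both videos are audio-normalised and free of language.

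Finally, silence in section 2.2.3 is not a denial of matching, and the 1:2 ratio could be read as extending it to Group C. That is possible, but it needs Group B to mean something other than its own definition. The mismatch with the abstract remains.

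**Conclusion.** The abstract states a design property, age and sex matching of all 200 peers, that the methods provide for Group B only. This rests on the text alone, with no assumption, and the ambiguous ratio in section 2.3 adds to it.

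The statistical consequence is conditional and modest. The A–C comparison is still adjusted for age and sex. Residual confounding from the video change arises only if three things hold together: Groups A and C differ in the share under 6, the video affects the outcome, and age is entered as a straight line. Under those assumptions and a 0.5 SD step it is about 0.03 to 0.14 SD, at most about one standard error, with type I error of 5% to 15%. It concerns the smartphone outcomes only.

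**What to change.** 1. In section 2.2.3, state that Group C will have an age and gender distribution similar to the autistic group, by frequency matching that includes the split between 3–5 years and 6 years and over. Otherwise, limit the abstract's matching statement to Group B.
2. In section 2.3, say which group or groups the matching and the 1:2 ratio refer to.
3. In models of prepulse inhibition, habituation and general sensorimotor behaviour, include video version (3–5 versus 6 and over) as a factor alongside age. If Group C has almost no children under 6, this term is estimated mainly from the other group and assumes the same step in both, which is a further reason for item 1.

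Cost: simple quota tracking, possibly slower Group C recruitment, and one model term. Item 1 must be settled before Group C is enrolled; item 3 can be settled at any time before analysis.
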